### Annual Follow-up Questionnaires

Annual follow-up questionnaires will include incidence of conditions and diseases, as well as selected instruments from the baseline and 6-month follow-up questionnaires. Additional items may be added in response to the evolving research literature on COVID-19 and that in other fields. Table 1 provides the anticipated data collection schedule.

### Registry and Ancillary Studies

During enrollment participants were given the option of providing contact information for follow-up questionnaires, which also enrolls them in the CHAMPS Registry. The CHAMPS Registry enables recruitment of eligible individuals for clinical trials of interventions relevant to COVID-19 or other disorders or conditions, as well as for ancillary studies of basic behavioral research or observational studies that require new data collection. Anticipated ancillary studies include a detailed assessment of lifestyle factors, interactions with family life, and wellness interventions. Ancillary study proposals will be reviewed by the CHAMPS Steering Committee for relevance, scientific interest, and participant burden.

### Analysis

#### Data Management and Quality

Data are collected through the web-based Qualtrics system. SPSS (IBM Corporation) and SAS (SAS Institute, Inc) will be used for data analysis. Initially, we will perform an exploratory analysis to establish patterns of missingness and distributions of the variables being measured. The registry data will be characterized with descriptive analyses, including frequency distributions, prevalence rates of COVID-19 testing and SARS-CoV-2 infection, and means and standard deviations of scores on the scales measuring work environment, general health status, anxiety, depressive symptoms, social support, traumatic stress, social support, sleep quality, and stress. Multiple logistic and linear regression methods will be used to assess baseline associations of health and well-being with estimates of exposure to COVID-19 infection and COVID-19–related stress at work. Models will be adjusted for sex, age, race/ethnicity, and job classification. Other preliminary explorations of associations between measured variables will be performed to aid the development of substudies from the registry. Follow-up health status questionnaires will enable analysis of associations between incident health events and baseline variables.

Narrative responses to the final question on the questionnaire will be analyzed using a deductive approach and thematic content analysis techniques. Multiple investigators will read the narratives provided by participants to perform coding of the significant statements made by participants. After multiple readings, investigators will generate data categories and clusters of statements and will develop themes.

#### Aim 1

We will determine whether essential workers with higher COVID-19 service exposure burden will experience higher rates of stress, depression, anxiety, and substance use than the general population at the time they enroll in CHAMPS, and higher than in similar populations before the COVID-19 pandemic. We will compare exposure by type of service, occupation, and place of service (eg, clinical setting or community), controlling for age, self-reported sex, and race. We will conduct analyses to identify mediators, such as racial status, and moderators, such as proactive coping and resilience.

#### Aim 2

We will determine whether the severity of mental health symptoms will be associated with changes in the prevalence of SARS-CoV-2 infections by geographic region.

#### Aim 3

We will ascertain whether exposure to COVID-19 service burden will affect physical and mental health over time and how these are influenced by psychosocial variables (eg, stress, depression, anxiety, burnout). We will analyze whether longitudinal health outcomes are associated with type of service; severity and duration of mental health symptoms; and age, sex, race, and other variables. We anticipate that some analyses will depend on the adequacy of the sample sizes in various demographic subgroups.

#### Aim 4

We will obtain longitudinal data to determine whether mental health symptoms will persist longer among participants with more severe symptoms and whether these symptoms will be associated with higher incidence of physical health conditions.

#### Aim 5

We will ascertain the extent to which the thematic contents of the narrative responses to the final question of the questionnaires are correlated with measures of distress (stress, anxiety, depression, burnout) and moderated by measures of resilience. We will ascertain whether thematic content is a moderator or mediator of health outcomes and is associated with retention of participants over time.

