**Methods:**

The study cohort is a convenience sample recruited nationally through communities, professional organizations, networks, social media, and snowball sampling. Recruitment took place for 13 months to obtain an estimated sample of 2762 adults who provided self-reported information administered on the web through structured questionnaires about their work environment, mental and physical health, and psychosocial factors. Follow-up questionnaires will be administered after 6 months and annually thereafter to ascertain changes in health, well-being, and lifestyle. Participants who consented to be recontacted form the longitudinal cohort and the CHAMPS Registry may be contacted to ascertain their interest in ancillary studies for which they may be eligible.

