**Results:**

The study was approved by the Institutional Review Board and launched in May 2020, with grants from Travere Therapeutics Inc, McKesson Corporation, anonymous donors, and internal funding from the M. Louise Fitzpatrick College of Nursing at Villanova University. Recruitment ended in June 2021 after enrolling 2762 participants, 1534 of whom agreed to participate in the longitudinal study and the registry as well as to be contacted about eligibility for future studies.

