## Methods

### Study Components

CHAMPS consists of three components: (1) a cross-sectional study of respondents who consented to participate in a single assessment of health; (2) a longitudinal study of participants who consented to repeated waves of data collection; and (3) a registry comprised of participants who enrolled in the longitudinal study. The registry serves as a source of study participants who may be eligible for future ancillary observational studies as well as randomized clinical trials.

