### Informed Consent

An internet link provided access to the informed consent document that described the purpose of the study, time required to complete the questionnaire, duration of the study, and options for cross-sectional or longitudinal study participation. An affirmative consent response opened the baseline questionnaire. At the end of the initial survey, participants were asked to provide their email contact information for the longitudinal study and registry, which would be used to provide them with future questionnaires and information about studies for which they might qualify. The consent form also stated that information would be used only for medical research and shared only with other medical researchers. Participants were informed that they could end participation at any time.

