## Results

A review of the published literature on relationships between stressful life events and health led to the hypothesis that stress experienced by essential workers during the COVID-19 pandemic would affect their health status over time. In response, CHAMPS was designed to ascertain work-life experience during the first year of the pandemic, exposure to stress, and self-reported mental and physical health, as well as to determine effects of service during the pandemic on health over the subsequent 5 years. The CHAMPS longitudinal cohort serves as a registry for recruiting participants in future ancillary studies. After IRB approval, 2762 participants were enrolled between May 2020 and June 2021, with 1534 providing contact information for future studies and follow-up questionnaires.

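### The baseline descriptive analyses are assigned to the registry, which the article defines as 1534 of the 2762 people enrolled

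*Protocol article*

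**What the plan says.** The Study Components section lists three parts. The first is "a cross-sectional study of respondents who consented to participate in a single assessment of health", the second is a longitudinal study with repeated waves, and the third is "a registry comprised of participants who enrolled in the longitudinal study". The Registry and Ancillary Studies section gives the route of entry: "participants were given the option of providing contact information for follow-up questionnaires, which also enrolls them in the CHAMPS Registry".

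The counts agree wherever they appear. The abstract describes an "estimated sample of 2762 adults who provided self-reported information administered on the web", "1534 of whom agreed to participate in the longitudinal study and the registry". The Results section reports that "2762 participants were enrolled between May 2020 and June 2021, with 1534 providing contact information for future studies and follow-up questionnaires".

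On the order of events, the Informed Consent section says: "An affirmative consent response opened the baseline questionnaire". The request for an email address for the longitudinal study and registry came only once that survey was finished.

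The Data Management and Quality section then says: "The registry data will be characterized with descriptive analyses, including frequency distributions, prevalence rates of COVID-19 testing and SARS-CoV-2 infection". The sentence continues with means and standard deviations for work environment, general health, anxiety, depressive symptoms, social support, traumatic stress, sleep and stress.

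**The concern.** A term that the article defines narrowly is attached to an analysis that belongs to a wider group. The measures listed were put to everyone who consented, but the population named is the subset that later agreed to be recontacted. An analyst following the sentence literally would build the baseline tables on the registry alone, and people who took part only in the single assessment would not appear in them.

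Two things are at stake. The first is precision, because the denominator is smaller than it needs to be. The second is selection: people chose whether to leave contact details after answering the symptom scales, so the choice may be related to the quantities being described. The Limitations section covers people who decline to take part and retention over time, but not this opt-in step. Because the baseline regressions and Aim 1 name no population, descriptive tables on 1534 could also stand beside baseline comparisons on 2762 with nothing to tell the reader why the denominators differ.

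**Working it through.** The article gives no power, precision or sample-size calculation, so there is no derived figure to reproduce. The check is one of definitions, followed by simple arithmetic.

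**Which group the listed measures come from.** Table 1 places anxiety, depression, social support, sleep, traumatic stress and COVID-specific stress at T0; social support and COVID-specific stress are collected at no other time. The section on demographic data, general health and infection places general health and infection status at enrollment. The Measures section puts work environment in the baseline questionnaire. The article does not say separately when testing history was asked. None of the measures that Table 1 first collects at T1 (for example resilience, burnout, eating habits) is in the descriptive list. The list is therefore essentially the content of the baseline questionnaire, which opened to every consenting respondent.

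**Inputs.** Enrolled: N = 2762 (abstract; Results). Registry and longitudinal study: R = 1534 (same places).

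**Number left out.**
- 2762 − 1534 = 1228
- 1228 / 2762 = 0.4446, or 44.5%
- 1534 / 2762 = 0.5554, or 55.5%

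**Precision.** The ratio of standard errors, registry to all enrolled, is sqrt(2762/1534) = 1.34 at any common prevalence. The 95% half-width is 1.96 × sqrt(p(1−p)/n). The article gives no prevalence, so p is assumed:

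| Assumed p | n = 1534 | n = 2762 |
|---|---|---|
| 10% | 1.5 points | 1.1 points |
| 20% | 2.0 points | 1.5 points |
| 30% | 2.3 points | 1.7 points |
| 50% | 2.5 points | 1.9 points |

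**Selection.** Prevalence among all enrolled is p_all = 0.5554 × p_registry + 0.4446 × p_non-registry. Hence p_registry − p_all = 0.4446 × (p_registry − p_non-registry). The article reports nothing by recontact status, so the difference is assumed:

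| Assumed opt-in difference | Shift in registry-only prevalence |
|---|---|
| 2 points | 0.9 points |
| 5 points | 2.2 points |
| 10 points | 4.4 points |
| 15 points | 6.7 points |

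At an assumed prevalence of 30%, the shift equals the registry half-width when the difference is 2.29 / 0.4446 = 5.2 points. Below that, sampling error is the larger of the two; above it, selection is.

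**The case against.** The strongest reply is that the word is used loosely. The article calls the whole project the CHAMPS Study and Registry, so the registry data could mean the full data set. Alternatively, the sentence may only promise a profile of the recruitment pool, without excluding a description of everyone else. Nothing in it says that only registry members will be described. In addition, the population for each table is often left to a full protocol or SAP, and neither is shown.

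The loose reading cannot be ruled out, but it conflicts with the definition under Study Components and with the use of the word later in the same paragraph, where the registry is the source of substudies. If all enrollees are meant, the sentence still contradicts the definition and needs the same correction. If a profile of the recruitment pool is meant, the Analysis section contains no stated description of the full baseline sample. The point does not depend on what an SAP might add, because the mismatch lies in a sentence that the article itself states.

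Three stronger readings are tempting and should be resisted.

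- A reader might infer that the baseline regressions and the Aim 1 comparison with the general population are also confined to 1534. The sentence covers only descriptive analyses. The regression sentence names no population, and Aim 1 refers to workers when they enroll, without mention of the registry.
- A reader might infer that the baseline prevalences will be biased by a material amount. The documents give no basis for any opt-in difference, so neither the size nor the direction of a shift is known, and it may be small.
- A reader might infer that 44.5% of the baseline data would be discarded. That figure is a share of people enrolled. Completion of the scales among the 1228 is not reported, and the article expects some missingness.

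**Conclusion.** The point holds as a contradiction between a defined term and the analysis attached to it. Followed literally, the only stated descriptive analysis of the baseline measures omits 1228 of 2762 enrollees. The counts and the standard-error ratio of 1.34 follow directly from the article, provided that the 1228 completed the scales as often as the 1534 did; with poorer completion, the loss of precision would be smaller. The half-widths rest on assumed prevalences, and the shifts on assumed opt-in differences.

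The article never attaches the number 2762 to the cross-sectional study by name. That all 2762 belong to it is the natural reading of the abstract, Study Components and Informed Consent taken together. If that component were read as only the 1228 single-assessment respondents, registry-only tables would still leave them out.

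The loss of precision is modest. The avoidable selection step is the better reason to act, and the sentence should be corrected because doing so is nearly free. The conclusion concerns the baseline descriptives alone. It does not reach the regressions, Aim 1 or attrition in the longitudinal analyses.

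**What to change.** In Data Management and Quality, replace the opening words of the sentence, which name the registry data, with: the T0 data of all enrolled participants (n=2762). Show the registry and longitudinal subset (n=1534) in a parallel column of the same tables, with the number who answered each item, so that opt-in selection and missingness can both be seen. Keep the 1534 as the population for measures first collected at T1 or later.

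Naming the population for the baseline regressions and for each part of Aim 1 would be a helpful clarification, but it does not correct an error.

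The cost is one phrase and one table column. The baseline data are already collected.

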The effects of stress on long-term physical and mental health can take many years to become manifest. Military combat deployment [23,24] and elevated symptoms of posttraumatic stress disorder (PTSD) in civilians have been associated with increased risk of hypertension, myocardial infarction, and stroke [25,26]. Longitudinal trends show that the likelihood of developing multiple physical symptoms over time is higher for those who were deployed in combat than those without combat experience [27].

Research on the effects of stress on the COVID-19 workforce [9,18] is underway but is in its early stages [28], with mixed results [29]. Some studies have noted the potential importance of resilience in response to stress, including in health care workers [30], but adequate supporting data on the role of resilience in response to stress are lacking [31]. The COVID-19 pandemic experience of essential workers provides an opportunity to develop new information on the influence of sustained stress on the short- and long-term physical and mental health of the workforce involved in providing health care or to support health care personnel, as well as on the potential influence of aspects of resilience and its role in moderating the effects of stress.

Based on the extensive body of literature on the psychosocial influences on health, it is likely that the COVID-19 pandemic will have deleterious effects on the health of health care workers and support staff in a broad range of professions [32]. Over time, as COVID-19 treatments and management improve and infection rates decrease through public health measures and vaccination, we anticipate that sources of stress will decrease, resulting in a gradient of influence on health among health care workers who enroll in the COVID-19 Study of Healthcare and Support Personnel **(**CHAMPS) during later phases of the pandemic. The CHAMPS Study and Registry is designed to ascertain the time course and magnitude of these changes on the long-term mental and physical health of essential workers in the health care environment.

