### Objectives

The objective of the CHAMPS Study and Registry is to assess the short- and long-term physical, social, and behavioral health of personnel (“essential workers”) involved in supporting or delivering care for patients with COVID-19. Included are first responders, maintenance and support staff working in clinical settings, and health care professionals of all specialties and services. At enrollment, baseline data were obtained on the study participants’ working environment, lifestyle, and mental and physical health. Subsequent waves of data collection will obtain follow-up information after 6 months and then annually through 2024. The study was approved by the Villanova University Institutional Review Board (IRB) in May 2020.

The primary objectives of the CHAMPS study are to (1) determine the extent to which working in health care affects future physical and mental health; (2) evaluate trends over the time course of the evolving pandemic; (3) identify exposure variables that are associated with incident changes in health over time; and (4) identify factors that influence short- and long-term health. Specific hypotheses include the following:

Measures of mental health symptoms of anxiety, traumatic stress, depression, insomnia, disordered eating, resilience, burnout, and poor self-reported health will be more prevalent in essential workers than in the general population and greater in magnitude than reported in similar populations before the COVID-19 pandemic.The severity of mental health symptoms will be associated with prevalence of SARS-CoV-2 infection rates in the geographic region in which the study participants work.Mental health symptoms will persist longer among study participants with more severe symptoms.Essential workers who report elevated symptoms of anxiety, traumatic stress, or depression will experience exacerbation of existing physical health conditions over time and higher incidence of new physical health conditions.Severity and progression of mental and physical health conditions will be exacerbated by the degree of perceived exposure to adverse working environments, such as availability of personal protective equipment, extended working hours, and adequacy of staffing levels.

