### Participants and Recruitment

Eligible participants were adult essential workers involved in health care. For the purposes of the CHAMPS study, essential workers were defined as adult (aged 18 years or older) health care personnel, support personnel, and first responders working in any health care facility or in the community. Included were those working in facilities that are involved in patient care, such as hospitals, clinics, private practices, or screening facilities; those directly involved in patient care (eg, physicians, nurses, phlebotomists, respiratory therapists, pharmacists); laboratory staff; service employees (office staff, maintenance, housekeeping, food service); individuals working in long-term care facilities; and first responders (eg, police officers, firefighters, emergency medical technicians, paramedics). Collectively, we refer to these as “essential workers.” Enrollment took place over 13 months, from May 2020 through June 2021, throughout the United States.

Recruitment included advertising through local and national professional and trade organizations, news, social and professional media, alumni organizations, and word of mouth to describe the study and disseminate the internet link that provided access to the informed consent form and study questionnaires. Professional and trade organizations were identified and contacted. Website posts, e-newsletters, and social media were used to reach members of eligible occupations, with news or social media posts either by their group administrators or by the study team. The wider social media universe was reached through posts on university channels on various platforms, university-affiliated influencer posts, and a limited paid media campaign. Social media posts and outreach to organization leaders continued periodically throughout the recruitment period.

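### The baseline exposure models leave out enrolment date and region, which the plan itself expects to be related to health, so pandemic phase and place can confound the burden-symptom associations

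*Protocol article*

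**What the plan says.** All references are to the protocol article.

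- **Baseline models.** *Analysis, Data Management and Quality* plans logistic and linear regression to "assess baseline associations of health and well-being with estimates of exposure to COVID-19 infection and COVID-19–related stress at work". The covariates are then listed: "Models will be adjusted for sex, age, race/ethnicity, and job classification". The list has no open-ended term.
- **Aim 1.** Exposure is compared by type of service, occupation and setting, "controlling for age, self-reported sex, and race".
- **Spread in time and place.** *Participants and Recruitment*: "Enrollment took place over 13 months, from May 2020 through June 2021, throughout the United States". Table 1 has one baseline assessment (T0) per person, so each person's T0 falls at some point in that window.
- **Phase and health.** *Rationale*: "we anticipate that sources of stress will decrease, resulting in a gradient of influence on health among health care workers who enroll" in later phases of the pandemic.
- **Region and symptoms.** Hypothesis 2 under *Objectives*: "The severity of mental health symptoms will be associated with prevalence of SARS-CoV-2 infection rates in the geographic region" where the participant works.
- **Exposure score.** *Exposure Assessment* and Table 2 add six one-point items to a 9-item work-stress scale. Three of the six are the participant's own diagnosis, a diagnosed close contact, and caring for COVID-19 patients.

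**The concern.** A confounder is related to both exposure and outcome and is not a consequence of the exposure. By the article's own expectations, enrolment date and region are related to the outcome. They are plausibly related to the exposure score as well. Having had a diagnosis, or knowing someone who has, becomes more likely the later a person enrols, and both items, like COVID-19 care, plausibly follow local infection. Neither variable is in the models that relate score to symptoms.

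A coefficient for service burden could then partly reflect when and where people answered, and not only the conditions they worked under. Workers with equal burden who enrolled in May 2020 and in May 2021, or in a heavily and a lightly affected area, would be treated as exchangeable given demographics and job. The same applies to Aim 1's comparison of exposure across occupations and settings, if the mix of occupations recruited shifted over the window or between regions.

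**Working it through.** The article gives no figure to reproduce: no effect size, significance level or power. The check is therefore of the text first, then an illustration on stated assumptions.

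**Step 1. Is each link in the text?**

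| Link | Source | Status |
|---|---|---|
| Date to health | Rationale, gradient by enrolment phase | Stated as expected |
| Region to symptoms | Objectives, hypothesis 2 | Stated as a hypothesis |
| Date to exposure | Exposure Assessment items; Principal Considerations expects the long enrolment to widen the range of exposures | Expected for the range; inferred for the items |
| Region to exposure | Exposure Assessment items | Inferred |
| Date or region in the baseline or Aim 1 covariates | Data Management and Quality; Aim 1 | Absent |

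**Step 2. What does omission do in general?** Take standardised exposure X, symptoms Y and phase P, with no true effect of X on Y. Let a = corr(X, P) and b = corr(P, Y). Leaving P out gives X a false coefficient of about a × b. With N = 2762 (the enrolled sample), its standard error is about 1/√2762 = 0.019. The values of a and b and the two-sided 5% test are assumptions. Results come from 2000 simulated data sets per row.

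| a | b | a × b | Simulated mean coefficient, P omitted | False positives, P omitted | False positives, P included |
|---|---|---|---|---|---|
| -0.1 | -0.1 | 0.01 | 0.011 | 7.9% | 4.5% |
| -0.2 | -0.2 | 0.04 | 0.040 | 56% | 5.8% |
| +0.2 | -0.2 | -0.04 | -0.040 | 55% | 4.7% |
| -0.3 | -0.3 | 0.09 | 0.090 | 99.5% | 4.8% |

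Rows two and three show why the sign is unknown. If the score falls with time (the work-stress scale, on the Rationale's expectation), a is negative. If it rises (the diagnosis and contact items), a is positive. The planned score contains both kinds of component.

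**Step 3. Something closer to the planned score.** A six-item index, built from the one-point items without the 9-item scale, was simulated 400 times per scenario with N = 2762. Assumptions: uniform enrolment, no true effect, time trends in the items (for example, diagnosed contact rising from 20% to 70%), and symptoms falling by 0.2, 0.3 or 0.5 SD over the window.

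| Symptom trend | False positives without date | With date |
|---|---|---|
| 0.2 SD | 11% | 5% |
| 0.3 SD | 8% | 4.5% |
| 0.5 SD | 21% | 3.5% |

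The dip from 11% to 8% is within simulation error. The standard errors are √(0.11 × 0.89/400) = 1.6 points and √(0.08 × 0.92/400) = 1.4 points, so the difference of 3 points has a standard error of about √(1.6² + 1.4²) = 2.1 points. The full score, including the work-stress scale, was not simulated.

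**Step 4. Cost of adjusting.** Adding P multiplies the variance of the exposure coefficient by about 1/(1 - a²). For a = 0.2 this is 1/0.96 = 1.042, so standard errors rise by about 2%. For a = 0.3 it is 1/0.91 = 1.099, or about 5%.

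**The case against.** **Phase may act only through exposure.** The Rationale describes sources of stress falling and health following. On that path calendar time is a source of exposure variation, which the long enrolment is meant to supply, and adjusting for it gives up part of that contrast. This is fair as far as it goes: the Rationale alone does not state a direct path from phase to symptoms. But date and region lie upstream of exposure. If they act only through it, adjusting costs precision and does not bias the estimate. If they also act by other routes, omission does bias it. Hypothesis 2 ties symptoms to regional infection itself, and a work-stress scale plus six yes/no items is unlikely to capture every route.

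**Time and region are handled elsewhere.** Trends over the pandemic are a primary objective, and Aim 2 asks whether symptoms are associated with "changes in the prevalence of SARS-CoV-2 infections by geographic region". These are separate questions. Nothing carries date or region into the exposure models.

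**A condensed article leaves detail to the full plan.** That would answer silence, but here specific covariates are named. A fuller plan may extend the list; as stated, it omits both variables.

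Three stronger readings are tempting and are not supported:

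- *Aim 2's standard errors ignore clustering by region.* No model is stated for Aim 2, and the regression sentence concerns baseline exposure associations. Any inflation figure would also need an assumed number of regions, an assumed intraclass correlation, and infection constant within region over 13 months.
- *The longitudinal models exclude calendar date.* Aim 3 ends its covariates with an open reference to other variables, so date is not ruled out.
- *The bias is large and its direction known.* Taken alone, the contact item under the Step 3 trends has a false slope of -(0.5/12)/(0.45 × 0.55) = -0.168 SD per SD of symptom decline, or -0.034 to -0.084 SD for declines of 0.2 to 0.5 SD. That is one item, not the planned score, and the work-stress scale may pull the other way.

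**Conclusion.** The point holds for the baseline exposure models and Aim 1, and no further. The named covariates omit two variables that the article itself expects to be related to health and that plausibly drive several exposure items, so the burden-symptom associations are open to confounding by pandemic phase and place. That conclusion rests on the text, plus the inference that diagnosis, contact and COVID-19 care depend on time and place.

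The size and sign are unknown. The 8% to 21% for the six-item index, and the wider range in Step 2, show what omission could do under assumed trends and correlations. They are not estimates for this study. The change is worth making because adjustment is cheap whether or not the confounding proves material.

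**What to change.** Add two terms to the baseline exposure models and to the Aim 1 comparisons:

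1. questionnaire completion date, as calendar month or a smooth spline;
2. region, or local infection prevalence at the completion date.

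Report each exposure estimate with and without these terms, so that readers can see how much of the association is shared with phase and place. Keep the covariates already named.

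No new data collection should be needed. *Questionnaires* says geographic questions are asked, and responses come through a web-based system, so completion dates should be on file (an assumption). Local prevalence, if chosen, would need linkage to an outside series; region alone would not. The cost is a few degrees of freedom and somewhat wider intervals, about 2% to 5% in the exposure standard error if its correlation with phase is 0.2 to 0.3.
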